### 2.5. Attrition and Adherence

Attrition will be considered in case of: two consecutive absences or three alternate absences during the training sessions; changes in medication throughout the intervention; missing post-intervention or follow-up evaluations; illness that blocks continuity in the study. Adherence strategies will be used, such as telephone contact with participants, in order to remind them of the evaluation and intervention sessions. The hours offered will be flexible and possible problems that may interfere with the participation and continuity in the intervention will try to be prevented or resolved.

### 2.6. Screening

Study participants will be submitted to screening and an initial visit before being assessed for primary and secondary outcomes. A structured evaluation will be carried out, including sociodemographic data; time since diagnosis; disease severity according to the modified Hoehn and Yahr Clinical Staging Scale (Hoehn and Yahr, 1998; Goetz et al., 2004); medication doses used; levodopa equivalent daily dose (LEDD); symptoms of depression and anxiety, measured by the Hospital Anxiety Depression (HAD) scale; freezing of gait, assessed by the Freezing of Gait Questionnaire (FOG-Q) (Giladi et al., 2009); and type of disease, classified as akinetic-rigid, tremulant or mixed. Although of tremor-dominant and nontremor-dominant subtypes are the most comonly system used to defining Parkinson's disease subtypes, the participant's classification as postural instability gait disorder (PIGD) phenotype (or akinetic-rigid) has been used to specify a nontremor-dominant subtype (Marras, 2015). In this study, the participant's classification for PIGD score will be described based on “walking and balance” and “freezing” items of part II of Movement Disorder Society Unified Parkinson's Disease Rating Scale scores (MDS-UPDRS), and the “gait”, “freezing of gait” and “postural stability” items of part III of MDS-UPDRS scores (Jankovic et al., 1990). TD/PIGD scores will be used for all patients and calculate by dividing mean tremor subscores (2.10, 3.15a, 3.15b, 3.16a, 3.16b, 3.17a, 3.17b, 3.17c, 3.17d, 3.17 and 3.18) by mean PIGD subscores (2.12, 2.13, 3.10, 3.11 and 3.12) (Stebbins et al., 2013). Values equal to 1.15 classifiles the patient as TD subtype, whereas values equal to 0.90 represent PIGD. The patient will be classified as indeterminate subtype if the ratio between mean TD and mean PIGD valeus will be between 0.90 and 1.15 (Stebbins et al., 2013). The Mini-Mental State Examination (MEEM) will be applied in order to characterize the sample (Folstein et al., 1975). We will investigate lateral dominance aspects using the Edinburgh Handedness Inventory (Oldfield, 1971), and collect anthropometric data such as head circumference, inter-tragus and nasion-inion distance, height, weight and body mass index (BMI).

Screening will assess primary and secondary baseline outcomes. These assessments will be repeated at the endpoint (after the 12 sessions) and follow-up (after 1 month). The safety of tDCS application will be assessed at each session, by collecting information on perceived sensations, possible discomfort or adverse effects (Brunoni et al., 2011). All assessments will be conducted by physicians and physiotherapists with expertise in management of PD and application of specific scales for cognitive and motor assessment of people with PD.

### 2.7. Outcomes

The primary outcome will be functional mobility, measured using the Timed Up and Go test (Podsiadlo and Richardson, 1991), to stand up from a chair at the command: “Walk 3 meters, walk along a demarcated course, turn around and walk back to the chair, then sit down”. For secondary outcomes, the following instruments will be used to assess executive function: (1) Wisconsin Card Sorting Test (WCST) to assess planning, cognitive flexibility, working memory, monitorization, inhibition of perseverations, and aspects related to executive function (Heaton and Staff, 1993); (2) Stroop Test, to assess selective attention, inhibition, cognitive flexibility, processing speed, fluid intelligence and the semantic system (Lezak et al., 2004, Strauss et al., 2006); (3) Trail Making Test (TMT), to evaluate the ability to draw lines between consecutive numbers from 1 to 25 (Bowie and Harvey, 2006); (4) Verbal Fluency Test to assess semantic and phonemic fluency in 1 min (Brucki and Rocha, 2004); and (5) Montreal Cognitive Assessment(MoCA), to evaluate overall cognitive and executive function (Van Uem et al., 2016).

The following scales will be used to assess motor function: (1) Dynamic Gait Index (DGI), to assess eight aspects of gait as well as dynamic balance (Shumway-Cook et al., 2000); (2) 10-meter walk test, to estimate gait speed by recording the average time the patient takes to cover a distance of 10m in three attempts (Peters et al., 2013); (3) Borg Scale, to guide physical activity intensity level and measure perceived exertion during session training (Borg, 1982); (4) Sit-to-stand (STS) test; (5) Kinematics of Gait, to analyze movement using the Qualisys Motion Capture System (Qualisys Medical AB, 411 13, Gothenburg, Sweden). This system records the spatio-temporal variables of gait, as well as the angular variations of the hip, knee and ankle joints; (6) MiniBESTest, to measure aspects of static and dynamic balance (Franchignoni et al., 2010); (7) Revised Movement Disorder Society-Sponsored Revision of the Unified Parkinson's Disease Rating Scale (MDS-UPDRS), to assess motor function (Goetz et al., 2008); and (8) Short FES-I, to measure the level of confidence in performing daily activities, in addition to identifying fear of falling and possible social isolation (Kempen et al., 2008). All the instruments used to assess the primary and secondary outcomes are described in Table 1.

**Table 1 T1:** Primary and secondary outcome measures.

	**Outcome measures**	**AV-1**	**AV-2**	**Follow-UP**
**Primary outcome measure**				
Fucntional mobility	Timed Up and Go Test (TUG)	X	X	X
**Secondary outcome measure**				
Cognitive function	Wisconsin Card Sorting Test (WCST)	X	X	X
	Stroop Test (ST)	X	X	X
	Trail Making Test (TMT)	X	X	X
	Verbal Fluency Test (VFT)	X	X	X
	Montreal Cognitive Assessment (MoCA)	X	X	X
Motor function	Dynamic Gait Index (DGI)	X	X	X
	Ten Meter Walk test (10MWT)	X	X	X
	Borg Scale	X	X	X
	Sit-to-stand Test (STS-5x)	X	X	X
	Kinematic gait variables	X	X	X
	MiniBESTest	X	X	X
	MDS-Unified Parkinson's Disease Rating Scale (MDS-UPDRS II and III)	X	X	X
Participation	ShortFES-I	X	X	X

### 2.8. Safety

In order to control adverse effects, patients will be asked about the sensations experienced during the session in terms of “tingling,” “burning,” “headache,” and “sleepiness” and other discomforts, which will be scored as intensity (1-none, 2-mild, 3-moderate, and 4-strong), and whether this effect is related to stimulation on a 5-point Likert scale (Brunoni et al., 2011); where, 1 represents no relation and 5 a strong relation. If any injury or strong discomfort is identified, therapy will be stopped and specialized medical assistance provided, at no cost to the participant. Any adverse effects will be documented along with symptom severity and duration, as well as the cause of the adverse effect.

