### 2.2. Participants

The following inclusion criteria will be applied: being diagnosed with idiopathic Parkinson's disease by a neurologist based on definitive evidence of responsiveness to levodopa at the start of the disease and the history of progressive hypokinesia with asymmetric onset. PD will be diagnosed based on Parkinson's Disease Society Brain Bank (PDSBB) criteria, as described in Hughes et al. (1992): age between 40 and 70 years, with no distinction for sex, schooling level or other sociodemographic characteristics; disease staging between 1.5 and 3, according to the modified Hoehn and Yahr scale (Hoehn and Yahr, 1998); undergoing regular pharmacological treatment with levodopa (equivalent dose > 300 mg) or taking antiparkinsonian medication, such as anticholinergics, selegiline, dopamine agonists, and COMT (catechol-O-methyl transferase) inhibitors for at least 4 weeks prior intervention; score of more than 24 points on the Mini-Mental State Examination (Folstein et al., 1975); not exhibiting other associated neurological diseases; and no musculoskeletal and/or cardiorespiratory changes that could compromise gait. The exclusion criteria will be diagnosis of atypical Parkinson's disease; neuropsychiatric comorbidities; convulsions, metal clips and/or pacemaker; deep brain stimulation implant; history of epilepsy; neurosurgery; traumatic brain injury; alcohol abuse or drug dependency; associated diseases of the peripheral or central nervous system; undergoing physical therapy at another location; inability to walk 10 meters; presence of important dyskinesia that prevents the participant from sitting in a chair; abnormal and persistent increase in systemic blood pressure before or during training, after three measurements taken 5 min apart-Cut-off: systolic blood pressure ≥ 140 mm Hg and/or diastolic ≥ 90 mm Hg (Malachias et al., 2016); not understanding any of the training protocol stages; chemical scalp treatment within the previous 30 days, and experiencing severe pain and/or discomfort that precludes performing the proposed activities.

History of falls in the last 12 months will be used to classify individuals into “non-fallers” (number of falls ≤ 1) or “recurrent fallers” (number of falls ≥ 2). Freezing of gait episodes will be screened and classified according to the dual-task screening questionnaire (Strouwen et al., 2014).

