### 3.2. Dual-Task and Its Relationshiap With Executive Function

The direct relationship between bradykinesia and mental flexibility and operational memory sustains the premise that EF in PD is correlated with motor function (Domellöf et al., 2011) and becomes a strong correlation as the disease progresses (Ebersbach et al., 2013).

Cognitive demand is considered a concurrent effort while people with PD and motor fluctuations walk (Hobson and Meara, 2004; Rochester et al., 2007; Plotnik et al., 2009; Michely et al., 2015). On the other hand, DT induces an increase in cholinergic activity in the dorsolateral prefrontal cortex, thalamus and basal ganglia (Yogev et al., 2005), which makes DT training important despite the greater risk of falling.

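### Solicited safety questions are aimed at tDCS, which both arms receive; falls, the harm the article links to dual-task training, are not prospectively asked about in either arm

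*Protocol article*

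**What the plan says.** - **What is asked.** Section 2.8 says that "patients will be asked about the sensations experienced during the session in terms of" tingling, burning, headache and sleepiness, plus other discomforts. Intensity is scored on four levels, and the patient also rates "whether this effect is related to stimulation on a 5-point Likert scale".
- **When, and for what purpose.** Section 2.6 presents the check as one on stimulation: "The safety of tDCS application will be assessed at each session, by collecting information on perceived sensations, possible discomfort or adverse effects".
- **Open clauses.** Section 2.8 adds "Any adverse effects will be documented along with symptom severity and duration, as well as the cause of the adverse effect", and "If any injury or strong discomfort is identified, therapy will be stopped" with medical help provided. Neither clause is limited to stimulation, and neither has an end date.
- **Contrast between arms.** Under section 2.4 both groups receive active tDCS with gait training, and the experimental group adds dual-task work.
- **Falls.** Section 3.2 comments on the cholinergic response to dual tasking, "which makes DT training important despite the greater risk of falling". The Introduction also says that doing cognitive and motor tasks together may raise fall risk, with fractures and trauma as consequences. The only fall data named are in section 2.2: "History of falls in the last 12 months will be used to classify individuals" as non-fallers or recurrent fallers.
- **Follow-up.** Section 2.1 sets T1 at 4 to 7 days and T2 at 30 days after the last session. Table 1 lists no fall count at any assessment.

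**The concern.** A safety item can inform the randomised comparison only if it could plausibly differ between the arms. Scalp sensations and their attribution to stimulation are expected to be similar in both arms, because both receive the same current. The component that differs is walking under cognitive or manual load, and the harm the article associates with it is falling. That harm has no prospective question.

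If the trial reports a mobility benefit from adding dual-task training, readers will want the matching account of falls. If falls were not asked about in the same way in both arms, that account cannot be rebuilt at analysis. Unprompted recording may also differ by arm, because experimental-group patients are observed while doing demanding tasks with stops and errors counted.

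**Working it through.** **1. Setting the passages side by side**

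| Question | What the article provides |
|---|---|
| Which component differs between arms? | Dual-task exercises (2.4) |
| What do the named safety items target? | Sensations during the session (2.8) |
| What is attribution rated against? | Stimulation only; no rating for treadmill or dual-task training (2.8) |
| When are the questions asked? | At each session (2.6); none described at T1 or T2 |
| Where do falls appear as data? | 12-month history before entry, for classification (2.2) |
| Is any repeated measure related to falls? | Short FES-I (confidence, fear of falling) and MiniBESTest (balance), at all three assessments (2.7, Table 1); neither counts falls |
| Could a fall still be recorded? | Yes, under the general adverse-effect clause or the injury clause (2.8) |

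The general clause asks for symptom severity, duration and cause. These descriptors suit a symptom better than an event such as a fall without injury, and nothing in the clause prompts for such a fall or a near-fall. Tables 2 to 4 record stops and spilled water during dual-task work, but not falls, and they apply only to the experimental group.

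**2. What full ascertainment could show**

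The article gives no fall rate or safety target, so there is no plan figure to reproduce. The input is 28 patients per group (2.10). With no fallers among n patients, the exact one-sided 95% upper bound on the proportion who fall is 1 − 0.05^(1/n).

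- n = 28: 1 − 0.05^(1/28) = 0.101, about 10%.
- n = 23 (half of the 46 that section 2.10 says are needed): 1 − 0.05^(1/23) = 0.122, about 12%.

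The patient is the right unit. Counting sessions gives 28 × 12 = 336 and 1 − 0.05^(1/336) = 0.0089, or 0.9% per session. That figure treats repeated sessions from the same person as independent and assumes full attendance, so it should not be used as the measure of precision.

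**3. Whether a falls comparison could be powered**

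The fall rates here are assumptions. With two-sided alpha 0.05, n = 28 per arm and p̄ = (p1 + p2)/2, the normal approximation is

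power = Φ{ [|p2 − p1| − 1.96 √(2p̄(1 − p̄)/n)] / √[(p1(1 − p1) + p2(1 − p2))/n] }.

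- 10% v 20%: (0.100 − 0.187)/0.0945 = −0.92, power 18%.
- 10% v 30%: (0.200 − 0.210)/0.1035 = −0.09, power 46%.
- 20% v 40%: (0.200 − 0.240)/0.1195 = −0.34, power 37%.

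For 80% power, the experimental-group rate would have to be about 42% against 10%, or about 56% against 20%. A falls comparison would therefore be descriptive even with perfect collection.

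**The case against.** The strongest objection is that this is a condensed article. The adverse-event form may well name falls, and section 2.8 contains nothing false. Staff are present during training, so a fall on the treadmill would ordinarily be seen, and that is when the arms differ most in exposure. Section 2.6 also collects information on adverse effects at each session, so recording is not purely spontaneous. The article makes no safety claim for dual-task training, and the Introduction ties fall risk to performing concurrent tasks, not to an after-effect of training.

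Much of this stands, and it limits the point. A reader might infer that safety collection ends at the last session. The article does not say so: the per-session schedule belongs to the tDCS check, and the general clause has no end date. A reader might also infer that the trial cannot compare falls at all. That goes too far, because a fall, especially one with injury, could be documented under section 2.8 in either arm.

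What does not stand is that condensation disposes of the matter. The article does not leave safety to another document. It sets out its solicited symptoms, an intensity scale and an attribution scale, and directs them at the shared component. Staff observation does not cover falls between sessions or after training, and no question about those is described.

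**Conclusion.** The point holds in a limited form. Falls are not systematically and prospectively ascertained in both arms through T2, although the article itself associates dual-task work with falling. Any between-arm account would depend on general recording that may be incomplete and may differ by arm.

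The consequence is a gap in the harms description. It does not affect the primary outcome, its analysis or the sample size. Its scale is set by 28 patients per arm: even complete data with no fallers would exclude only rates above about 10% per patient, and power for assumed differences such as 10% v 20% or 10% v 30% is 18% to 46%. The bound assumes that all 28 are followed; with 23 it is about 12%. The conclusion also assumes that the full protocol adds no fall question beyond what the article describes. It is a worthwhile, inexpensive improvement, and its timing matters because falls that go unrecorded cannot be recovered later.

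**What to change.** 1. Add a fall and near-fall item (yes/no, number, any injury) to the per-session safety questions, worded identically in both arms.
2. At the existing T1 and T2 visits, ask both arms about falls since the last contact.
3. Report fall counts and the proportion of patients with at least one fall by arm, with the patient as the unit. Give confidence intervals and label the comparison descriptive.
4. If the full protocol already collects this, state it in section 2.8 and no further change is needed.

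The cost is one item on the session questions, one question at two planned visits, and slightly more data entry. No extra visit or sample-size change is needed, and no powered test of falls should be implied.

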### 2.9. Intervention

#### 2.9.1. tDCS

Patients will be submitted to 12 training sessions, 3 times a week, for 20 min (Bello and Fernandez-Del-Olmo, 2012), simultaneously to the rehabilitation program. Direct current (2 mA) will be transferred by a neurostimulator (Neuroelectrics Starstim eight system^®^), portable, battery operated, attached to the participant's body by means of a waist pack and positioned on the back to facilitate the monitoring and movement of the arms during treadmill training. Electrodes with dimensions of 5 × 7 cm (35 cm2) will be positioned on the scalp covered by sponges electrode soaked with 0.9% saline solution. The anodic electrode will be placed on F3 to stimulate the left dorsolateral prefrontal cortex, and the cathode electrode will be positioned over the right contralateral supraorbital frontal cortex (respectively F3 and Fp2 in the international 10–20 system Electroencephalography placement) (Homan et al., 1987; Antal et al., 2017; Lefaucheur et al., 2017). We chose this montage to match previous studies of tDCS in PD patients.

In order to verify the configuration of the electrode selected, the distribution and flow of the current for the tDCS configuration will be simulated using SimNIBS 2.1 (SimNIBS software, http://www.simnibs.org) and MNI (Montreal Neurological Institute) coordinates.

#### 2.9.2. Rehabilitation Program

The participants will perform 12–20 min treadmill gait training associated to dual task exercises+tDCS, 3 times a week (Experimental Group) or treadmill gait training+tDCS (Control Group). If patients exhibit altered vital signs, they will be asked to remain seated and try to relax. If the situation persists, the patient will be instructed to visit their physician.

#### 2.9.3. Dual-Task Training Protocol (DTTP)

The dual-task training protocol (DT) will consist in cognitive exercise categories: verbal fluency, mental screening tasks, discrimination, decision-making and reaction time tasks, which will be associated to treadmill gait training (Sousa et al., 2016). Verbal commands will focus on the following: (1) large strides; (2) heel strike; (3) raising the knees while walking (Kelly et al., 2012).

DT will be conducted using activities with three levels of difficulty (Tables 2–4), such as (i) mental screening tasks involving addition and subtraction, such as counting backwards from 100 and subtracting 3 or 7, while walking; (ii) verbal fluency tasks in which the participant is asked to name items that start with a particular letter or have a common characteristic (farm animals, words with the letter A, B, C, etc) while walking; (iii) discrimination and decision-making tasks, such as saying YES when the word “strawberry” is heard and NOTHING when no fruit is heard; (iv) fastening buttons and a zipper while walking; (v) Looking down and then up while walking; (vi) walking with head turns associated with motor or cognitive disorders; (vii) dual-task of carry a tray while walking (Mehrholz et al., 2015). Participants will only evolve from one level to the next when performance on the previous level is free of error. Thus, progression toward better performance of both the participant and the task will be based on the time that the participant will spend walking on the treadmill, i.e., increasing the walking speed or time on the treadmill in each block, performing the greatest number of words, presenting greater accuracy in decision-making, and reducing response time (Strouwen et al., 2014). At the end, participants will be asked to report the functional difficulties experienced during DT training.

**Table 2 T2:** Dual-task training at difficulty level 1.

**Task**	**Task description**	**Outcome measurement**	**Task limitations**
Counting backwards from 100	Subject walks while counting backwards from 100	- Number of calculations concluded. - Number of incorrect calculations. - Gait speed.	Depending on ability, may be more difficult for some participants than others.
Walking while carrying a tray with only one empty glass	The subject walks while carry a tray with one empty glass	- Gait speed. - Number of stops.	Involving the upper limbs may affect gait pattern. Difficulty depends on the amount of water in the glass.
Naming items in general that start with a particular letter while walking (the participant chooses and indicates the category of the item to list)	The subject walks while naming items that start with a particular letter of any category chosen and indicated by the participant.	- Gait speed. - Number of words generated.	Depending on ability, may be more difficult for some participants than others.
Walking forward saying YES when they hear the word “strawberry”	Subjects walk while listening to a list of fruits and says “YES” when they hear the word “strawberry”.	- Gait speed. - Number of correct answers. - Number of errors.	Depending on ability, may be more difficult for some participants than others.
Getting keys and a wallet out of a pocket and change the pocket side.	Subject walks while moving objects from one pocket to another.	- Gait speed. - Number of stops.	Involving the upper limbs may affect gait pattern.
Fastening buttons and a zipper while walking	Subjects walks while Fastening a zipper.	- Number of calculations concluded - Number of incorrect calculations - Gait speed.	Depending on ability, may be more difficult for some participants than for others.
Looking from one side to another while walking	Subjects walk while turning their head from one side to another.	- Gait speed. - Range of head motion.	Head motion may change balance and gait pattern.

**Table 3 T3:** Dual-task training at difficulty level 2.

**Task**	**Task description**	**Outcome measurement**	**Task limitations**
Counting backwards from 100 and subtracting 3 while walking.	Subjects walk while counting backwards from 100 and subtracting 3.	- Number of calculations concluded. - Number of incorrect calculations. - Gait speed.	Depending on ability, may be more difficult for some participants than others.
Walking while carrying a tray with at least one glass filled with water while say peron's names.	The subjects walks while carry a tray with at least one glass filled with water while say person's names.	- Gait speed. - Number of stops. - Amount of water spilled.	Involving the upper limbs may affect gait pattern. Difficulty depends on the amount of water in the glass.
Walking while naming items that have the same characteristics (marine animals, names of city, farm animals etc).	The subjects walks while naming items that have the same characteristics: farm animals.	- Gait speed. - Number of words generated.	Depending on ability, may be more difficult for some participants than others.
Walking forward saying “YES” when they hear the word “strawberry” and “No” when they hear the word “banana”.	Subjects walk while listening to a list of fruits and say “YES” when they hear the word “strawberry” and says “No” when hear the word “banana”.	- Gait speed. - Number of correct answers. - Number of mistakes.	Depending on ability, may be more difficult for some participants than others.
Getting a wallet out of pocket counting coins and moving them from one pocket to another.	Subjects walk while moving coins from one pocket to another	- Gait speed. - Number of correct answers. - Number of mistakes.	Depending on ability, may be more difficult for some participants than for others.
Fastening buttons and a count buttons while walking.	Subjects walk while fastening buttons and count buttons.	- Gait speed. - Number of buttons concluded.	Depending om ability, may be more difficult for some participants than for others.
Looking down and the up while walking and saying object names in general	Subjects walk while looking down and then up and sayings object names in general.	- Gait speed. - Number of correct objects.	Head movements may change balance and gait pattern mainly when damage the visio (lookink up).

**Table 4 T4:** Dual-task training at difficulty level 3.

**Task**	**Task description**	**Outcome measurement**	**Task limitations**
Counting backwards from 100 and subtracting 7 while walking.	Subjects walk and move around obstacles while counting backwards from 100 and subtracting 7.	- Number of calculations concluded. - Number of incorrect calculations. - Gait speed.	Depending on ability, may be more difficult for some participants than others.
Walking while carrying a tray with at least two glasses filled with water while naming the cars models.	The subjects walk while carry a tray with at least two glasses filled with water while the naming cars models.	- Gait speed. - Number of stops. - Amount of water spilled. - Number of words named	Involving the upper limbs may affect gait pattern. Difficulty depends on the amount of water in the glass.
Naming items that have the same characteristics (farm animals with only two legs.	The subjects walks while naming items that have a common characteristics: farm animals with only two legs.	- Gait speed. - Number of words named. - Number of stops.	Depending on ability, may be more difficult for some participants than others.
Walking forward saying “YES” when they hear the word “watermelon” and say “No” when they hear all another fruit names pronounced by researcher	Subjects walks while listening to a list of fruits and say “YES” when they hear the word “watermelon” and “NO” when they hear all another fruit names pronounced by researcher.	- Gait speed. - Number of correct answers. - Number of stops. - Number mistakes	Depending on ability, may be more difficult for some participants than for others.
Getting a wallet out of a pocket, counting coins and moving them from one pocket to another.	Subjects walk while moving coins from one pocket.	- Gait speed. - Number of correct answers. - Number of mistakes.	Depending on ability, may be more difficult for some participants than for others.
Fastening buttons, count buttons and calculate the sum of the coins while walking.	Subjects walk while fastening buttons, count buttons and calculate the sum of the coins.	- Number of buttons concluded. - Gait speed.	Depending on ability, may be more difficult for some participants than for others.
Looking down and then up while walking and sayings words that begin with the letter “F”.	Subjects walk while and sayings words tha begin with the letter “F”.	- Gait speed. - Number of correct answers (words that begin the letter “F”).	- Head movements may change balance and gait pattern mainly when damage the vision (looking up).

